## 16.5 Serious Adverse Events that do not require reporting

Some particular SAEs may not be reported to the sponsor, for example if they are expected to occur on a regular basis and offer no further new information to the safety profile or are related to the disease area of the participants. They will be reported if the frequency or severity of these events is unusual. These events will continue to be recorded in the CRF.

## 16.6 Reporting Urgent Safety Measures

If any urgent safety measures are taken the CI/ PI shall immediately and in any event no later than 3 days from the date the measures are taken, give written notice to the relevant REC and Sponsor of the measures taken and the circumstances giving rise to those measures.

## 16.7 Protocol deviations and notification of protocol violations

A deviation is usually an unintended departure from the expected conduct of the study protocol/SOPs, which does not need to be reported to the sponsor. The CI will monitor protocol deviations.

A protocol violation is a breach which is likely to effect to a significant degree –  
 (a) the safety or physical or mental integrity of the participants of the study; or  
 (b) the scientific value of the study.

The CI and sponsor will be notified immediately of any case where the above definition applies during the study conduct phase.

## 16.9 Trust incidents and near misses

An incident or near miss is any unintended or unexpected event that could have or did lead to harm, loss or damage that contains one or more of the following components:

- a. It is an accident or other incident which results in injury or ill health.
- b. It is contrary to specified or expected standard of patient care or service.
- c. It places patients, staff members, visitors, contractors or members of the public at unnecessary risk.
- d. It puts the Trust in an adverse position with potential loss of reputation.
- e. It puts Trust property or assets in an adverse position or at risk.

Incidents and near misses will be reported to the Trust through DATIX as soon as the individual becomes aware of them.

A reportable incident is any unintended or unexpected event that could have or did lead to harm, loss or damage that contains one or more of the following components:

- a) It is an accident or other incident which results in injury or ill health.
- b) It is contrary to specified or expected standard of patient care or service.
- c) It places patients, staff members, visitors, contractors or members of the public at unnecessary risk.
- d) It puts the Trust in an adverse position with potential loss of reputation.
- e) It puts Trust property or assets in an adverse position or at risk of loss or damage.

1034 **17 MONITORING AND AUDITING**

1035 The Chief Investigator will ensure there are adequate quality and number of monitoring  
1036 activities conducted by the study team. This will include adherence to the protocol,  
1037 procedures for consenting and ensure adequate data quality.

1038  
1039 The Chief Investigator will inform the sponsor should he/she have concerns which have  
1040 arisen from monitoring activities, and/or if there are problems with oversight/monitoring  
1041 procedures.

1042  
1043  
1044  
1045 **18 TRAINING**

1046 The Chief Investigator will review and provide assurances of the training and experience of  
1047 all staff working on this study. Appropriate training records will be maintained in the study  
1048 files.  
1049

1050 **19 INTELLECTUAL PROPERTY**

1051  
1052 All intellectual property rights and know-how in the protocol and in the results arising directly  
1053 from the study, but excluding all improvements thereto or clinical procedures developed or  
1054 used by each participating site, shall belong to UCL. Each participating site agrees that by  
1055 giving approval to conduct the study at its respective site, it is also agreeing to effectively  
1056 assign all such intellectual property rights ("IPR") to UCL and to disclose all such know-how  
1057 to UCL with the understanding that they may use know-know gained during the study in  
1058 clinical services and teaching to the extent that such use does not result in disclosure of UCL  
1059 confidential information or infringement of UCL IPR.

1060 **20 INDEMNITY ARRANGEMENTS**

1061  
1062 University College London holds insurance against claims from participants for harm caused  
1063 by their participation in this clinical study. Participants may be able to claim compensation if  
1064 they can prove that UCL has been negligent. However, if this clinical study is being carried  
1065 out in a hospital, the hospital continues to have a duty of care to the participant of the clinical  
1066 study. University College London does not accept liability for any breach in the hospital's  
1067 duty of care, or any negligence on the part of hospital employees. This applies whether the  
1068 hospital is an NHS Trust or otherwise.

1069 **21 ARCHIVING**

1070  
1071 UCL and each participating site recognise that there is an obligation to archive study-related  
1072 documents at the end of the study (as such end is defined within this protocol). The Chief  
1073 Investigator confirms that he/she will archive the study master file at UCL for the period  
1074 stipulated in the protocol and in line with all relevant legal and statutory requirements. The  
1075 Principal Investigator at each participating site agrees to archive his/her respective site's  
1076 study documents for 10 years and in line with all relevant legal and statutory requirements.

## 1077 22 PUBLICATION AND DISSEMINATION POLICY

1078

1079 Study results will be published in peer-reviewed academic journals and also presented at  
1080 public and scientific conferences. This work will also be highlighted on media channels, both  
1081 traditional (TV, radio) and internet including UCL/ICN webpages and Twitter feeds.

1082

## 1083 23. Covid-19 safety precautions

1084

1085 This study will involve direct interaction between researchers and participants given the need  
1086 for researchers to undertake some cognitive testing face to face. To minimize risk of CV19  
1087 infection, the following precautions will be taken.

- 1088 • Researchers or participants will not be permitted to be involved if
  - 1089 ○ They have active CV19 infection
  - 1090 ○ They have been knowingly exposed to anyone with active CV19 infection
- 1091 • Researchers and participants will use PPE (disposable gloves, face mask) where  
1092 appropriate
- 1093 • Wherever possible, social distancing will be observed

1094

1135 **25. APPENDICES**

1136 Include here supplementary information and documents that will support the protocol and  
1137 information contained therein, e.g. PIS, ICF, schedule visit, assessment tools, delegation  
1138 log, case report forms, questionnaires, scales, tables, charts, diagrams, manufacturer's  
1139 brochures.

1140

1141

1142

1143

[figure not shown][figure not shown]

## DOCUMENT HISTORY

| Updated version no. | Effective date | Authorship | Section changed | Summary of changes |
|---------------------|----------------|------------|-----------------|--------------------|
| 1                   | 05/09/2024     | [name]    | N/A             | N/A                |

## 1. ACRONYMS AND DEFINITION OF TERMS

| Acronym | Meaning                                                  |
|---------|----------------------------------------------------------|
| AE      | Adverse Event                                            |
| BSGI    | Bangor Goal Setting Interview                            |
| CONSORT | Consolidated Standards for Reporting Trials              |
| CV19    | Covid-19                                                 |
| CTU     | Clinical Trials Unit                                     |
| DSH     | Data Safe Haven                                          |
| ITT     | Intention to Treat                                       |
| MAR     | Missing at Random                                        |
| MCAR    | Missing Completely at Random                             |
| MI      | Multiple imputation                                      |
| MRI     | Magnetic Reasoning Imaging                               |
| NHS     | National Health Service                                  |
| NWORTH  | North Wales Organisation for Randomised Trials in Health |
| PI      | Principal Investigator                                   |
| RCT     | Randomised Controlled Trial                              |
| SAE     | Serious Adverse Event                                    |

|     |                           |
|-----|---------------------------|
| SAP | Statistical Analysis Plan |
| UCL | University College London |
| WS1 | Work Stream 1             |
| WS2 | Work Stream 2             |

## 2. STATISTICAL ANALYSIS PLAN AUTHORSHIP

The Statistical analysis plan (SAP) has been authored by [name], Senior Statistician with input from [name] (Principal Statistician), [name] (Project Manager), [name] (Research Assistant), [name] [name] (Co-applicant) and [name] (Chief Investigator).

The quantitative Statistical analysis described in this document relates to WS2 of the trial (RCT) and will be completed by [name] at NWORTH CTU with oversight from [name]. Analysis of WS1 will be reported separately. Analysis will be conducted blinded, and an initial blinded results report will be produced and sent to the team. Once all blinded analysis listed in the SAP has been conducted the statisticians will be officially unblinded following NWORTHs SOPs, and further analysis on intervention data, listed in section 6.5, 6.8 and 6.9 will be conducted.

## 3. INTRODUCTION

### 3.1 BACKGROUND AND RATIONALE

Cognitive impairment is recognised as a major component of long Covid, present in 25-75% of affected individuals, but little is known about the nature of this impairment, or how it can be treated. The associated loss of functional ability has major consequences for affected people, their families and the wider economy given the problems caused in terms of return to work. The aim of this study is to determine the nature of the cognitive impairment and deliver cognitive rehabilitation to help a return to normal life.

### 3.2 TRIAL AIMS AND OBJECTIVES

Workstream 2 will develop and test the effectiveness of a neuropsychological rehabilitation intervention to support recovery from cognitive Covid.

Aims:

- Can a neuropsychological rehabilitation programme (COVID Rehab) improve the cognitive and functional outcomes of people with cognitive Covid?

- What is the incremental cost-effectiveness of COVID-Rehab compared to standard clinical care for cognitive Covid?\*1
- What is the cost per quality-adjusted life year (QALY) of COVID Rehab compared to standard clinical care for cognitive Covid, and does this fall below the NICE threshold of £20,000 to £30,000 per QALY?\*

#### Objectives:

- To develop and test the effectiveness of a neuropsychological rehabilitation intervention programme for cognitive Covid (COVID-Rehab) to deliver improvements in clinically relevant outcomes including quality of life and functional ability.
- To investigate the incremental cost-effectiveness of the CIVIC-Rehab intervention compared to standard clinical care, using multiple measures of effect.\*

### 3.3 TRIAL DESIGN

WS2 – The second workstream will develop a suite of phenotype-specific and evidence-based neuropsychological rehabilitation packages targeted at the cognitive domains primarily affected in cognitive Covid, using functional and quality of life outcomes to measure treatment efficacy. This collection of strategies will be informed by outcomes from workstream 1 and co-produced in collaboration with a group of people living with cognitive Covid-19 (we will refer to this group as Experts by Experience). This will be a parallel individually randomised controlled trial, comparing the study intervention (cognitive rehabilitation) with the clinical standard of care (current clinical management pathways for long Covid, including treatment for fatigue, respiratory disorders, sleep, anxiety and depression).

### 3.4 PARTICIPANT POPULATION

Participants will be recruited from the cohorts of patients with long Covid and cognitive impairment seen in the Cognitive Disorders Clinics held at University Hospitals Sussex

---

 \*Health economic analysis will be conducted outside of NWORTH, the current SAP and associated report will not cover analyses associated with these aims and objectives.

NHS Trust (PI [name]), Southampton NHS Trust (PI [name]), and Greater Manchester Mental Health Trust (PI [name]). They will initially be approached by the local PIs or associated researchers working at each study site and informed consent for participation will be obtained.

Inclusion Criteria:

- Aged between 30 and 60 years
- Evidence of prior CV19 infection
  - *either* positive CV19 PCR
  - *or* positive CV19 antibody test
  - *or* acute symptoms consistent with the recognised core features of acute CV19 infection and post-acute symptoms consistent with the recognised core features of long Covid

Cognitive impairment persisting more than three months after the acute CV19 infection, defined in terms of subjective reports of cognitive decline post-infection.

Exclusion Criteria:

- Cognitive impairment prior to CV19 infection
- Occurrence of acute neurological disorder, such as stroke or encephalitis, that could give rise to cognitive sequelae.
- People who are on any medications that are considered by the study investigators to have significant adverse effects on cognition.
- A pre-existing major psychiatric or medical disorder that is considered by the study investigators to have potential to affect cognition.
- High alcohol intake
- Recreational drug use
- Loss of mental capacity such that the affected individual is unable to give informed consent.
- Participants will not be eligible for Workstream 2 if they do not exhibit significant impairment on baseline cognitive assessments, defined as impairment in two or more cognitive domains, as they will not gain from cognitive rehabilitation (i.e. for inclusion Scores  $\geq$  1 SD below age-adjusted mean in at least two of the following cognitive domains: immediate memory, visuospatial memory, language, attention, delayed memory, information-processing speed, executive functioning, inhibition, and verbal fluency)

- Participants with pacemakers or other implanted devices, those with metal foreign bodies (e.g. shrapnel from war injuries) and those who have had certain types of surgery will be excluded from the MRI substudy. Although MRI is not known to affect the unborn child, we will also exclude subjects who may be pregnant just to be on the safe side.

### 3.5 PARTICIPANT FLOW DIAGRAM

[figure not shown]

**Figure 1:** CICERO WS2 Participant Flow Diagram

## **4. STATISTICAL PRINCIPLES**

All those randomised will be included in the analysis based on an intention to treat (ITT) principal.

### **4.1 SAMPLE SIZE JUSTIFICATION**

A sample of 88 (44:44) will be required to detect an effect of 0.7 on the BGSI at 3 months with 90% power at a 5% significance level. Incorporating an attrition of 25% will require recruitment and randomisation of 118 participants (59:59). Therefore, 120 participants will be recruited from the same clinics. Participants in WS1 can if desired take part in WS2.

### **4.2 RANDOMISATION**

Randomisation will take place once consent and baseline data collection has been completed. Randomisation will be on a 1:1 allocation (intervention:control) via a secure online system hosted by NWOORTH, Bangor University. The system will employ a dynamic adaptive randomisation algorithm. The randomisation will be stratified for centre (London/Sussex/Southampton/Manchester). A member of the research team at UCL will enter the participants details into the web form and perform the randomisation, which will either display directly on screen, if the researcher is unblinded or notification of the randomisation result will be sent to the designated parties to organise ongoing contact.

### **4.3 LEVELS OF CONFIDENCE AND P-VALUES**

All statistical tests will be two-sided and performed using 5% level of significance. All confidence intervals presented will be 95%, unless stated otherwise.

Secondary outcomes will not be adjusted for multiple comparisons, as standard. The primary outcome is powered for at the significance level stated. Analysis of all secondary outcomes is considered exploratory, and any statements of results related to these outcomes will be reported appropriately.

### **4.4 COMPLIANCE/ADHERENCE**

There is no planned analysis for compliance and treatment adherence. Sensitivity analysis will be run on the number of intervention sessions received, see section 6.9 for further details.

## 4.5 PROTOCOL VIOLATIONS

Definition of protocol violations and deviations. Violation is an intended failure to adhere to the protocol such as wrong treatment being prescribed or administered or incorrect data being collected and documented. A protocol deviation is an unintended failure to adhere to the protocol and examples include errors in applying inclusion/exclusion criteria or missed follow-up visits due to error. Protocol deviations and violations will be monitored and detailed descriptively in the analysis report. If protocol deviation occurrences rise above 10% then sensitivity analysis as detailed in section 6.5 will be conducted. Some examples of protocol deviations which might occur in this study include;

- Patients not receiving randomised allocation.
- Ineligible participants being randomised.
- Participants receiving their BGSi goals after completing it at baseline.

*ITT is the expected standard for RCTs and demonstrates the effectiveness of the intervention in the pragmatic context. Per protocol will provide evidence of efficacy and if there is a large difference then there may be a difficulty in implementation of the intervention which needs fixing before the intervention would be adoptable by the NHS.*

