### 7.1 Power calculation

Evidence from the GREAT trial of cognitive rehabilitation in neurodegenerative disease using the same primary outcome Bangor Goal Setting Interview (BGSi) indicated an effect of approximately 0.8 in a population with dementia. This is likely to be an underestimation of the effect in this study as it is likely that the intervention will be more effective in people without neurodegeneration as seen in the population in the GREAT trial.

Assuming a minimally clinically important difference of 2 points (<https://www.thecopm.ca/faq/>) and a more conservative effect of 0.7 would require SD of the measure to be approximately 2.86. Baseline SD observed in the GREAT trial was 1.74, it is likely that variability in our sample is likely to be larger and therefore we can accommodate an Increase in variability of approximately 65%.

A sample of 88 (44:44) will be required to detect an effect of 0.7 on the BGSi at 3 months with 90% power at a 5% significance level. Incorporating an attrition of 25% will require recruitment and randomisation of 118 participants (59:59).

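### SAP 4.5 treats per-protocol results as evidence of efficacy and explains a large gap from ITT only as possible poor implementation, with no per-protocol set defined and no mention of selection

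*Combined protocol and SAP*

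**What the plan says.** SAP section 4 makes ITT on all randomised participants the analysis principle, and SAP 6.6 compares the arms on BGSI attainment at 3 months. An explanatory note at the end of SAP 4.5 assigns ITT to effectiveness in practice and then says: "Per protocol will provide evidence of efficacy and if there is a large difference then there may be a difficulty in implementation". The note adds that this difficulty would have to be put right before NHS uptake.

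The surrounding text bears on how that note would be used:

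- SAP 4.5 calls for a sensitivity analysis if deviations exceed 10% and refers to section 6.5 for it. Section 6.5 contains only descriptive statistics.
- Its three examples of deviations are failure to get the allocated arm, randomising someone ineligible, and a participant being given back the goals set at baseline.
- SAP 4.4 plans no compliance analysis, although Protocol 7.3 expects an adherence analysis to be detailed in the SAP.
- SAP 6.9 adds the number of sessions to the model. A further analysis drops anyone who had a session outside its window; missed sessions do not count for this.
- SAP 2 and 6.9 place the session-based analyses after unblinding.

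**The concern.** A per-protocol set is formed after randomisation, so its two arms need not be comparable. In this trial the exclusions could well be related to prognosis. The programme is ten one-hour sessions with tasks in between (Protocol 5.2.2), in a condition for which the trial itself measures fatigue and post-exertional malaise. Those who are kept may have been less ill or already recovering. Participants know their allocation and report the primary outcome themselves.

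The SAP names one reading of a large gap, implementation, and leaves out selection and inability to tolerate the programme. The hedge in the sentence covers implementation only; the statement about efficacy has none. If a null ITT result came with a favourable per-protocol result, a report following this note could describe the therapy as efficacious but hard to deliver. The data would fit a therapy with no effect and selective exclusion equally well.

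**Working it through.** **1. The plan's own figures.** SAP 4.3: "All statistical tests will be two-sided and performed using 5% level of significance". SAP 4.1: "A sample of 88 (44:44) will be required to detect an effect of 0.7", with "90% power at a 5% significance level". A two-sample t-test calculation gives 43.87, so 44 per arm, with power 90.1%. Attrition: 88 / 0.75 = 117.3, so 118. In Protocol 7.1, 2 points at an effect of 0.7 "would require SD of the measure to be approximately 2.86": 2 / 0.7 = 2.86. The same section says: "Baseline SD observed in the GREAT trial was 1.74". The ratio 2.86 / 1.74 is 1.64. All of this agrees with the documents, and the sample size is not in question.

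**2. Inputs for the bias.**
- True effect: zero.
- Participants per arm: 44 (analysed) and 59 (randomised), from SAP 4.1.
- SD range for conversion to BGSI points: 1.74 to 2.86, from Protocol 7.1. The first is a baseline SD from another population and the second an implied SD, so neither is an estimate for this trial.
- Share q of the intervention arm excluded: 10%, 20% and 30%. This is an assumption; 10% matches the trigger in SAP 4.5.
- Correlation ρ between adherence propensity and outcome: 0, 0.3 and 0.5. This is an assumption.
- Control arm left intact. This is an assumption; it matches the 6.9 window rule.

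**3. Formula.** If the lowest share q on adherence propensity is dropped from the intervention arm, then

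bias in SD units = ρ × φ(z_q) / (1 − q),

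where φ is the standard normal density and z_q the q-quantile.

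- q = 10%, ρ = 0.3: 0.3 × 0.1755 / 0.9 = 0.058
- q = 20%, ρ = 0.3: 0.3 × 0.2800 / 0.8 = 0.105
- q = 30%, ρ = 0.3: 0.3 × 0.3477 / 0.7 = 0.149
- q = 30%, ρ = 0.5: 0.5 × 0.3477 / 0.7 = 0.248

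**4. Simulation.** 20,000 runs per setting with an unadjusted t-test. A false benefit is a significant result in favour of the intervention, nominally 2.5%. Paired percentages are for 44 and 59 per arm.

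| Excluded | ρ | Bias (SD) | BGSI points, SD 1.74 to 2.86 | False per-protocol benefit | Per-protocol favourable, ITT not |
|---|---|---|---|---|---|
| 10% | 0.3 | 0.058 | 0.10 to 0.17 | 4.3%, 4.8% | 1.9%, 2.4% |
| 20% | 0.3 | 0.105 | 0.18 to 0.30 | 6.8%, 7.9% | 4.3%, 5.4% |
| 30% | 0.3 | 0.149 | 0.26 to 0.43 | 8.9%, 11.0% | 6.5%, 8.5% |
| 30% | 0.5 | 0.248 | 0.43 to 0.71 | 18.0%, 24.0% | 15.6%, 21.4% |

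At ρ = 0 the bias is zero, the false-benefit rate is 2.3 to 2.5%, and the last column is 0.5 to 0.9%. The ITT test rejects in 4.7 to 5.3% of runs (two-sided) throughout.

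**5. How many the window rule could exclude.** One out-of-window session is enough. If each of ten sessions has an independent chance p of being out of window (assumed), the excluded share is 1 − (1 − p)^10. This is 18% at p = 2%, 40% at p = 5% and 65% at p = 10%. Exclusions well above 10% are therefore possible, though scheduling slips need not be related to prognosis.

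**The case against.** The case for leaving the text alone is substantial. The sentence sits in an explanatory note and specifies no test. ITT is primary, implementation is offered only as a possibility and only for a large difference, and the deviation analysis runs only above 10%.

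A reader might infer more than the documents support, in three ways:

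- **That per-protocol means completers of all ten sessions against an untouched control arm.** No section says so. Two of the three listed deviations can occur in either arm, missed sessions are not among them, and attendance enters 6.9 as a covariate with everyone retained. Exclusions from both arms would bias less.
- **That the SAP lets a per-protocol result override a null ITT result.** Nothing says this.
- **That large false-positive rates are to be expected.** Keeping only 60% of the intervention arm with a correlation of 0.5 gives about 26% two-sided, but neither value is in the documents. At the 10% that SAP 4.5 does mention, the bias is small.

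The calculation is also unadjusted. A per-protocol analysis using the SAP 6.6 model would adjust for site, gender, age, education, baseline RBANS and baseline BGSI, and so remove part of the selection. The direction is not certain either: if recovered participants stopped early, the bias would reverse.

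These points limit the size of the problem. They do not remove it. The efficacy statement is unhedged, no section adds a warning about selection, fatigue and post-exertional malaise are not in the 6.6 model, and the 6.9 window rule acts on one arm only. With the set undefined and session data analysed after unblinding, the choice of whom to exclude stays open.

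**Conclusion.** The concern stands as a fault in interpretation and specification. SAP 4.5 gives an undefined, non-randomised comparison the status of efficacy evidence and offers one explanation for a gap from ITT where at least two others are plausible. The possible bias runs from zero, if exclusion is unrelated to prognosis, through about 0.06 SD (10% excluded, correlation 0.3) to about 0.25 SD (30%, 0.5). The last figure is 0.43 to 0.71 BGSI points, or 22% to 36% of the 2-point important difference in Protocol 7.1. Whether that would count as a large gap cannot be settled, because the SAP sets no threshold.

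These sizes rest on assumed exclusion shares and correlations, one-armed exclusion and no covariate adjustment. They show what could happen and do not forecast it. The primary ITT test, its error rate and the sample size are unaffected.

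**What to change.** 1. Replace the sentence in SAP 4.5. State that conclusions on benefit rest on ITT, and that any per-protocol result is supportive, open to selection bias, and not in itself evidence of efficacy or of an implementation problem.
2. Define the per-protocol set and its model before unblinding, and point the deviation analysis to a section that contains it instead of 6.5.
3. If an effect among those treated is wanted, estimate it with randomised arm as instrument. Prespecify the session threshold that counts as treated, and state the exclusion restriction (allocation affects the outcome only through reaching that threshold). The estimate is the ITT difference divided by the between-arm difference in the share treated, so a zero ITT difference gives a zero estimate. SAP 4.4 would need to change to match.
4. Tabulate baseline characteristics of included against excluded participants, with the Chalder fatigue score and DSQ-PEM, both already collected.

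The cost is a short SAP amendment and one extra table. The instrument-based interval will be wider than the per-protocol one, and partial attendance below the threshold may strain the exclusion restriction.
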